**Maintenance phase**

At the end of implementation for the last wave of clinics, all ten clinics will concurrently commence maintenance evaluation (Fig. 3). Technical support, however, will reduce after six months of intervention implementation. RH facilities will be assessed to determine their readiness for reduced technical assistance support using predefined metrics. Metric measures will include a review of number of providers trained and implementing SVA-SAT+TA, treatment completion rate, and experience of adverse events. The assessment will determine whether intervention implementation by facility personnel without the intervention of research personnel is maintained. Bi-annual facility level assessments will be done and they will include a review of infrastructure and staffing to see if there are changes in the preparedness across sites over the maintenance period*.*

**Outcome Variable:** Our primary study outcome is change in treatment completion rate among screen-positive women, comparing pre-and post-intervention periods. The impact of this work will be evaluated using the RE-AIM framework as follows (Table 4) :

- **REACH** refers to the number, proportion or representativeness of individuals or entities reached by an intervention. We will assess the number of providers trained within each clinic. If SVA-SAT + TA is adopted and implemented as intended, we expect the number of women receiving cervical cancer screening and treatment services to increase. We will abstract individual level program data and estimate the proportion of women aged 25-49 years seeking services in reproductive health clinics who are screened per month (target = 20%) and proportion of screen-positive women who complete treatment (target = 60%) comparing pre-implementation period to intervention periods. This will include women treated with cryotherapy, LEEP or any other procedure.

**Table 4: Summary of outcomes, by RE-AIM domain**

| RE-AIM Domain | Outcomes | Data source |
| --- | --- | --- |
| REACH | - Proportion of providers trained, and women screened per month | - Abstracted client records - Facility level data |
| EFFECTIVENESS | - Number of women screen-positive per month - Treatment completion rate among screen-positive women compared to pre-intervention (Primary) - Proportion of women with clearance of HPV 6 months post receiving TA treatment | - Facility level data - HPV test results from randomly selected women |
| ADOPTION | - Proportion of selected clinics incorporating thermal ablation into routine care through updated policies - Proportion of trained providers performing SVA_SAT +TA - Facility readiness | - Facility level data, Technical assistance reports - ORIC scores |
| IMPLEMENTATION | - Core components of the SVA-SAT+TA - Description of drivers of success/failure using CFIR constructs of interest | - Facility level data, Technical assistance reports - Key informant interviews |
| MAINTENANCE | - Proportion of clinics that continue to provide and sustain SVA-SAT+TA services 12,18 and 24 months after intervention implementation | - Facility level data |

- **EFFECTIVENESS** is a clinic and individual level measure that refers to whether the intervention had intended and unintended effects. We will determine whether the intervention is associated with a change in the number of screen-positive women identified per month and a substantial increase in treatment completion rate, comparing pre-and post-intervention periods.

Through an HPV-sub study, we shall assess fidelity of implementation of TA techniques by assessing for HPV clearance. We will collect HPV cervical swab prior to and 6 months post treatment to assess for clearance of type-specific HPV infection (target 60% HPV clearance) post-treatment on an estimate of 360 screen positive women treated with TA. HPV samples will be shipped to the UW/UON HIV/STD Research laboratory in Mombasa.

**Power and sample size** According to data on cervical cancer screening and preventive treatment for Kiambu County from 2017-2019, 20% of cervical cancer screening clients who screened positive received cryotherapy or LEEP. Routine data from our proposed study facilities show an average of 30 clients per month were screened at each facility in the first three months of 2020 (**Table 3**), corresponding to approximately 10% of eligible clients. The primary effectiveness outcome is the proportion of screen-positive women who receive same day ablation treatment. Assuming six-month waves, 30 clients screened per month and a 5% screen positive rate, we will have an average of 9 screen-positive women per facility per wave. Assuming an intracluster correlation coefficient of 0.2, alpha=0.05 and 20% treatment coverage pre-intervention, we will have 80% power to detect a three-fold increase to 60% treatment coverage using thermal ablation (R (v 3.6.3) package swCRTDesign (v 3.1)). We estimate that 90% of screen positive women will be eligible for ablative treatment.(49)

**Data analysis**: The primary analysis of proportion of screen positive women who are treated pre vs post- intervention. We will use weighted least square methods appropriate for this facility-randomized three-wave step wedge design, where all clinics begin in the control condition, We will consider the intervention effect to be fixed throughout the exposed period, but random effects per facility and wave. To analyze secondary outcomes of increase in proportion of trained providers (the **REACH** outcome) and increase in number screen-positive (secondary outcome) we will use the same analysis approach for the binary and count outcome. Exploratory analysis will examine potential effect modification of facility-level factors such as patient volume, patient to provider ratio, and women screened. Potential multi-level adjustment variables include individual-level factors such as age and access to resources. The HPV sub-study in women treated with TA will assess HPV clearance in HPV-positive women. Assuming 70% of screen-positive women test positive for HPV prior to TA (N = 140), the confidence interval for HPV clearance will be +/-8.1%

- **ADOPTION**

Our primary outcomes for adoption will be

1. the proportion of clinics incorporating TA into routine care through updated policies
2. Proportion of trained providers performing SVA-SAT +TA for screen positive women and
3. health facility readiness to implement SVA-SAT+TA.

The Organizational readiness for implementing change (ORIC) tool, will be used to measure the extent to which organizational members are psychologically and behaviorally prepared to implement organizational change, such as decisions to adopt interventions like SVA-SAT+TA.

Components of readiness which will be covered within the ORIC will include

1) change commitment, reflecting shared resolve to implement a change.

2) change efficacy, reflecting a shared belief in the collective capability to implement change.

To understand readiness for adopting SVA-SAT+TA, we will apply the validated ORIC assessment scale translated and adapted to this context after each implementation wave begins (typically within 1-3 months after start, so that participants are knowledgeable of the intervention but it is still relatively new). ORIC is a 12-item Likert-type scale, broken into domains of change commitment (4 items) and change efficacy (8 items), and has demonstrated reliability, content validity, structural validity, structural invariance, and known-groups validity in field application. We will apply the ORIC to 3 management team members of each intervention facility (n=30) and 6 frontline health workers per intervention facility (n=60). Analysis will test whether sufficient inter-rater reliability and inter-rater agreement exist to aggregate individual responses to the facility level. If tests do not justify aggregation, we will use a measure of intra-facility variability in readiness rather than a facility-level mean in our analysis. The resulting analysis will provide readiness profiles for each facility as they initiate implementation, which will complement adoption, implementation and effectiveness data in understanding the broader impact of SVA-SAT+TA.

- **IMPLEMENTATION** of SVA-SAT+TA will be measured at the organizational levels to establish consensus on the core components of the intervention as well as determine the drivers of its implementation success and failure. We will use a CFIR-guided lens to review and describe SVA-SAT+TA implementation across a heterogenous sample of health facilities (described above). A participant Informed Consent Form (ICF) will be offered before the interview process where we will seek to know experiences with SVA-SAT+TA implementation.
- CFIR will guide our examination of the implementation processes and adaptations across the different facilities as well as document determinants of success and failure. We will conduct small group discussion with health providers (n = 3) at each clinic and in-depth interviews with health managers (n = approximately 5) and screen-positive women ( 2 per clinic, n=20) at spread out over the intensive implementation wave. Interviewees will be purposively selected to capture diversity in health facilities (rural vs urban, large vs small size, government facility vs mission facility). Interview guides will include questions adapted from the CFIR question bank (cfirguide.org) to gather data about selected constructs from 4 of the established CFIR domains (Table 6). Outer setting constructs of interest will be captured via fields to identify critical external events. In addition, we will also attempt to capture newly identified constructs (and one additional domain) identified by Means, et al. Questions associated with these novel constructs will be piloted for understandability and appropriateness prior to data collection. Constructs of interest may be adapted based on the outcomes of Aim 1.

**Table 5: Potential questions to providers and managers by CFIR construct**

Additionally, at the end of each intensive implementation wave, we will administer a checklist among a small group of 3-5 healthcare providers per facility. The purpose of this checklist will be to evaluate the extent to which the deployed implementation strategies respond to the pre-identified barriers (Appendix 1). We shall include an end user satisfaction survey at each facility at the end of each wave.

Analysis**:** Interviews will be recorded, transcribed and analyzed using directed content analysis following a deductive approach, using the CFIR as a guiding framework.

Thematic analysis will be applied to analyze the open responses from healthcare providers on the administered checklist. This analysis will help us understand reasons behind the pre-identified barriers were both successfully and unsuccessfully addressed categorizing them into three level i.e., successfully, partially successful, and unsuccessful.

- **MAINTENANCE** is the extent to which an intervention and the benefits it generates are sustained over time. In the first six months of implementation we will have bi-weekly on-going technical support to health facilities. For 12 months thereafter, we will reduce visits by 50% among clinics that meet metrics for transition, we will then discontinue routine technical assistance visits, but only respond to facility requests as needed. Over this time, research staff will continue to abstract individual level programmatic data. We will continue to monitor the proportion of women aged 25-49 years seeking services in reproductive health clinics who are screened per month and proportion of screen-positive women who complete treatment. In addition, we will monitor the frequency of facility committee meetings. We anticipate that facilities will continue to implement SVA-SAT+TA because we will have utilized a participatory approach that builds ownership and organizational commitment and results in implementation of an intervention that is contextually fit.

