**Objective 2:**

**Deliver the SVA-SAT+TA intervention at scale in RH clinics and evaluate implementation using the RE-AIM framework**.

*Approach*: We will introduce the SVA-SAT+TA into RH clinics using a stepped-wedge study design and rigorously evaluate how effectively this intervention is disseminated and implemented. Key endpoints will include:

a) (REACH) Proportion of the clinics reached, providers trained;

b) (EFFECTIVENESS) Intervention effect on SVA-SAT process measures: number of screen positive women identified per month, treatment completion rate compared to pre-intervention, and the patient-level TA fidelity of implementation assessed by testing HPV clearance 6 months post-treatment among 360 randomly selected screen positive women treated with TA;

c) (ADOPTION) Proportion of the clinics incorporating TA into routine care through updated policies and trained provider in practice;

d) (IMPLEMENTATION) Determine core components of the SVA-SAT+TA intervention and describe drivers of success/failure using the Consolidated Framework for Implementation Research;

e) (MAINTENANCE) Proportion of clinics that continue to provide and sustain SVA-SAT+TA services 6-12 months after intervention implementation.

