Stakeholder meeting size will be approximately 30 – 40 persons who will be divided into three small groups to discuss determinants of implementation. To identify determinants of implementation from the workshop, the research qualitative team will summarize key points from small group deliberations and present these summary findings back to the stakeholders for consensus. We will use this feedback to refine our design to be compatible with facility workflow and systems, aligns with organizational culture and is agreeable to our stakeholders. In addition, we will use a checklist to evaluate the extent to which the deployed implementation strategies during the intensive implementation phase respond to the pre-identified barriers gathered at this stakeholder’s workshop.

***Aim 2:* Deliver the SVA-SAT+TA intervention at scale in RH clinics in Kenya and evaluate implementation using the RE-AIM framework**

Overview. At 10 reproductive health facilities in central Kenya, we will introduce the SVA-SAT + TA intervention developed and refined in Aim 1 in a stepped-wedge fashion and rigorously evaluate how effectively this strategy is disseminated and implemented. In three successive waves, with a new wave starting approximately every six months, we will roll out the intervention at 3-4 clinics per step (Fig 2). A final maintenance phase will permit evaluation of the stability of the intervention over time without direct study inputs.

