# **DATA**

The primary goal of this project is to develop a dissemination and implementation strategy to introduce SVA-SAT+TA and deliver the intervention in the reproductive health facilities at a scale

*Data Collection*

We will use computer-based or paper based data collection forms for research variables and link to medical records data captured through standard clinic systems (e.g. cancer of the cervix screening, intervention offered for the screen positive women). All data will be maintained in a secure location. Internal quality control reports will be run on a monthly basis.

We will use CFIR interview guide tool to assess barriers and facilitators to potential adoption, delivery and sustainment of the SVA-SAT + TA intervention

Baseline data collection on proportion of screen positive women getting treatment pre-implementation will be collected at least 6 months prior to initiation of the intervention

After initiation we will collect the following information

- Proportion of women screened per month
- Proportion of trained health care providers
- Treatment completion rates for screen positive women
- Proportion of women with clearance of HPV at month six post treatment (this will be done in a sub-study with approximately 360 women)
- Proportion of clinics that have incorporated TA into routine care
- Proportion of trained providers performing SVA-SAT+TA
- Description of drivers and facilitators using CFIR constructs of interest
- Proportion of clinics that continue to provide and sustain SVA-SAT+TA services 13, 18 and 24 months after implementation phase

*Analysis*

Qualitative analyses will identify and describe key themes and explore variation within themes. Descriptive content will be inductively assembled to form explanatory accounts.

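### The maintenance endpoint has three conflicting timings and the support period two conflicting lengths, so some stated time points cannot show sustainment without study support

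*Protocol*

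**What the plan says.** **Purpose.** The Aim 2 overview states: "A final maintenance phase will permit evaluation of the stability of the intervention over time without direct study inputs". The Maintenance phase section says the same of its assessment: "The assessment will determine whether intervention implementation by facility personnel without the intervention of research personnel is maintained". The justification for the stepped-wedge design, which appears in the Background and again under Aim 2, is softer. It speaks of maintenance once intensive support has been withdrawn.

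**Support schedule.** The MAINTENANCE item under Aim 2 (after Table 5) begins: "In the first six months of implementation we will have bi-weekly on-going technical support to health facilities". It continues: "For 12 months thereafter, we will reduce visits by 50% among clinics that meet metrics for transition". Routine visits then stop, and the team responds only to requests. No end of support is given for clinics that miss the metrics. Under the intensive implementation phase, the technical assistance item gives the duration as six to twelve months instead.

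**Timing of the endpoint.** Three places differ:
- Executive Summary, Objective 2: "Proportion of clinics that continue to provide and sustain SVA-SAT+TA services 6-12 months after intervention implementation"
- Table 4 of RE-AIM outcomes: "Proportion of clinics that continue to provide and sustain SVA-SAT+TA services 12,18 and 24 months after intervention implementation"
- Data section, data collection list: "Proportion of clinics that continue to provide and sustain SVA-SAT+TA services 13, 18 and 24 months after implementation phase"

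**Start of the phase.** When the last wave finishes implementation, "all ten clinics will concurrently commence maintenance evaluation".

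**The concern.** A maintenance result can speak to sustainment without the study only if it is measured after the study's routine visits have ended. The protocol gives three sets of time points, does not define the origin, and words it differently in the Data section. It also gives two lengths for the support period. A reader cannot tell which assessments are made with study staff still visiting and which are not.

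The question matters to this trial. The Background reports that earlier projects in Kenya introduced equipment and services that often lapsed when the project finished. The maintenance proportion is the evidence a national programme would use to judge whether this project differs. If supported and unsupported clinics are pooled, that proportion could make the service look more self-sustaining than the data can show. With ten clinics, each clinic moves it by 1/10 = 10 percentage points.

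**Working it through.** The protocol states no total for the support period, so there is no figure to reproduce. The check is date arithmetic.

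**Inputs.** Full visits for 6 months, then half-frequency visits for 12 months (MAINTENANCE item). Support of 6-12 months (technical assistance item). Three waves about six months apart with 3-4 clinics each (Aim 2 overview). Common maintenance start at the end of the last wave (Maintenance phase section). Assumptions: waves exactly six months apart and a six-month intensive phase. Figure 3 and the timeline are not available.

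**Step 1: end of routine visits.** 6 + 12 = 18 months after activation, for a clinic that meets the metrics on time.

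**Step 2: stated time points against month 18.**

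| Source | Stated (months) | Counted from activation | Counted from the end of a six-month phase |
|---|---|---|---|
| Executive Summary | 6-12 | 6-12: before month 18 | 12-18: before, up to the limit |
| RE-AIM Table 4 | 12, 18, 24 | before, at, after | 18, 24, 30: at, after, after |
| Data section | 13, 18, 24 | before, at, after | 19, 24, 30: all after |

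Taking both ends of the 6-12 window gives 8 listed points:
- All counted from activation: 4 before, 2 at and 2 after month 18.
- All counted from the end of the phase: 1 before, 2 at and 5 after.
- As worded, with only the Data section counted from the end of the phase: 3 before, 1 at and 4 after.

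The Executive Summary window does not pass month 18 on either count. Table 4's 24-month point is after it on both.

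**Step 3: position of each wave at the common maintenance start.** Count trial months from the first activation. Activations are at 0, 6 and 12, and the last wave's six months end at month 18. Routine visits left = activation + 18 − 18.

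| Wave | Activated | Routine visits end | Left at common start | 6 months later | 12 months later |
|---|---|---|---|---|---|
| 1 | 0 | 18 | 0 | 6 months off | 12 months off |
| 2 | 6 | 24 | 6 months | just ended | 6 months off |
| 3 | 12 | 30 | 12 months | 6 months left | just ended |

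If the 6-12 month window were counted from this common start, it would be off support throughout for wave 1, would begin as visits end for wave 2, and would still be on support until its last day for wave 3. A wave is 3-4 of ten clinics, or 30-40 percentage points of the proportion.

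**Step 4: sensitivity to the other stated duration.**
- With 12 months of support, visits end at trial months 12, 18 and 24. At the common start, wave 1 has been off for 6 months, wave 2 has just finished and wave 3 has 6 months left.
- With 6 months of support, visits end at 6, 12 and 18. The waves have been off for 12, 6 and 0 months.

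**Step 5: a point that does test unsupported sustainment.** Table 4's 24-month point, counted from activation, is 24 − 18 = 6 months after routine visits stop, for a clinic that transitions on time.

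**The case against.** Four objections deserve an answer.

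**Tapered support may be what was meant.** The design justification speaks only of intensive support being withdrawn, and the Maintenance phase section says openly that support is reduced after six months. On that aim, Table 4's points all qualify. This stands as a possible intention, but the Aim 2 overview and the Maintenance phase section promise more. The two aims need reconciling.

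**A reader might infer that most stated time points lie inside the support period.** That holds only if every point is counted from activation and month 18 itself counts as inside (4 + 2 = 6 of 8). The Data section, taken as worded with a six-month phase, gives months 19, 24 and 30, all outside. The support in months 6-18 is also reduced, not full. The documents support only that some points fall while visits continue.

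**A reader might infer that clinics missing the metrics keep fuller support and are then counted as maintained.** The metrics do include treatment completion, but the protocol does not say what happens to such clinics. This is a gap in the text and no stated rule. Likewise, that no clinic has been off support at the common start follows from the 18-month schedule and fails if support lasts at most 12 months.

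**Counting per clinic would remove the mixing.** This is correct for clinics on the same schedule, and Table 4 lists its points separately, so they need not be blended. The mixing arises only if assessment follows the common calendar start. The protocol does not say which applies.

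**Conclusion.** The point holds as a conflict to be reconciled. One RE-AIM endpoint has three timings with an undefined origin, and the support period has two lengths. On the 18-month schedule, the Executive Summary's window cannot show sustainment without routine visits on either per-clinic count. Table 4's 12-month point cannot do so if counted from activation. Under a common-calendar assessment, waves 1, 2 and 3 start with about 0, 6 and 12 months of routine visits remaining, so 6-7 of the ten clinics would still have visits scheduled.

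These figures assume a six-month intensive phase, waves exactly six months apart and clinics that transition on time. A shorter support period narrows the problem, as the sensitivity step shows. The documents do not establish that the reported proportion will be too high, only that its meaning is not fixed. Maintenance is a descriptive outcome, and the primary outcome, treatment completion, is not affected. The correction is still worthwhile because it decides what the trial can say about services after the study withdraws.

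**What to change.** 1. Reconcile the Executive Summary, RE-AIM Table 4 and the Data section to one set of time points with one defined origin.
2. Reconcile the technical assistance item with the MAINTENANCE item on the length of support, and say what happens to clinics that miss the transition metrics.
3. State one aim: sustainment after intensive support, or sustainment without routine study visits.
4. If the second, make the main maintenance result the proportion of clinics still providing the service at a fixed time, for example six months, after that clinic's routine technical-assistance visits stopped. For clinics that transition on time under the 18-month schedule, this is Table 4's 24-month point counted from activation.
5. Report earlier points separately, by each clinic's actual support status on the assessment date. Show clinics still receiving routine visits as their own category. They should not count as maintained without support, nor be scored as failures when services may be running.

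The cost is mainly protocol wording and recording the date of each clinic's last routine visit. Data abstraction and twice-yearly facility assessments are already planned. The unsupported proportion may be lower or rest on fewer than ten clinics. The Study Population section foresees at least 24 months of screening in the last clinics to activate, so a clinic that transitions late may not reach its assessment within the planned period.
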